**Supplementary Tables**

**Supplementary Table 1**: Breast screening uptake in 2021/22 and Index of Multiple Deprivation (IMD) quintile of selected services determined by the NHSBSP prior to the start of the study

| **Code** | **Service** | **Uptake^a^** | **IMD Quintile^b^** |
| --- | --- | --- | --- |
| FLO | Central and East London | 42% | 3 |
| EBA | North London | 54% | 2 |
| FBH | Outer NE London | 58% | 1 |
| MDU | Dudley, Wolverh. & SW Staffords. | 60% | 2 |
| DCB | Cambridge | 61% | 5 |
| CDO | Doncaster | 63% | 2 |
| LED | North and East Devon | 67% | 4 |
| ^a^ Year 2021/22 figure^3^  ^b^ 1 being the most deprived and 5 being the least deprived.. | | | |

**Supplementary Table 2**: Characteristics of women included in the services evaluation by NHSBSP service.

|  | Service name | | | | | | | | | | | | | |
| --- | --- | --- | --- | --- | --- | --- | --- | --- | --- | --- | --- | --- | --- | --- |
|  | Doncaster | | Cambridge | | North London | | Outer NE London | | Central and East London | | North and East Devon | | Dudley,Wolverh&  SW Staffords ^d^ | |
| Age (Mean, IQR) ^a^ | 60.0 | 54.0 – 65.0 | 54.4 | 50,0-59.0 | 59.4 | 55.0-64.0 | 58.8 | 54.0-64.0 | 58.5 | 54.0.63.0 | 59.1 | 55.0-65.0 | 58.4 | 52.0-64.0 |
|  |  |  |  |  |  |  |  |  |  |  |  |  |  |  |
| IMD (quintile) |  |  |  |  |  |  |  |  |  |  |  |  |  |  |
| 1: most deprived | 628.0 | (23.2%) | 83.0 | (3.6%) | 382.0 | (12.7%) | 1018.0 | (61.1%) | 514.0 | (22.1%) | 199.0 | (8.1%) | 1489.0 | (44.8%) |
| 2 | 422.0 | (15.6%) | 91.0 | (4.0%) | 780.0 | (25.9%) | 619.0 | (37.2%) | 1346.0 | (57.9%) | 306.0 | (12.4%) | 803.0 | (24.2%) |
| 3 | 564.0 | (20.8%) | 356.0 | (15.5%) | 743.0 | (24.7%) | 22.0 | (1.3%) | 304.0 | (13.1%) | 775.0 | (31.4%) | 525.0 | (15.8%) |
| 4 | 719.0 | (26.5%) | 679.0 | (29.5%) | 796.0 | (26.5%) | 2.0 | (0.1%) | 125.0 | (5.4%) | 616.0 | (25.0%) | 426.0 | (12.8%) |
| 5: least deprived | 359.0 | (13.2%) | 1051.0 | (45.7%) | 285.0 | (9.5%) | 0.0 | (0.0%) | 26.0 | (1.1%) | 542.0 | (22.0%) | 73.0 | (2.2%) |
| missing | 18.0 | (0.7%) | 41.0 | (1.8%) | 21.0 | (0.7%) | 4.0 | (0.2%) | 11.0 | (0.5%) | 30.0 | (1.2%) | 9.0 | (0.3%) |
|  |  |  |  |  |  |  |  |  |  |  |  |  |  |  |
| Prevalence and age |  |  |  |  |  |  |  |  |  |  |  |  |  |  |
| prevalent and <60 | 494.0 | (18.2%) | 1556.0 | (67.6%) | 762.0 | (25.3%) | 356.0 | (21.4%) | 805.0 | (34.6%) | 631.0 | (25.6%) | 1015.0 | (30.5%) |
| incident and <60 | 771.0 | (28.5%) | 190.0 | (8.3%) | 821.0 | (27.3%) | 570.0 | (34.2%) | 545.0 | (23.4%) | 616.0 | (25.0%) | 827.0 | (24.9%) |
| 60+ | 1445.0 | (53.3%) | 531.0 | (23.1%) | 1424.0 | (47.4%) | 734.0 | (44.1%) | 974.0 | (41.9%) | 1221.0 | (49.5%) | 1483.0 | (44.6%) |
| missing | 0.0 | (0.0%) | 24.0 | (1.0%) | 0.0 | (0.0%) | 5.0 | (0.3%) | 2.0 | (0.1%) | 0.0 | (0.0%) | 0.0 | (0.0%) |
|  |  |  |  |  |  |  |  |  |  |  |  |  |  |  |
| Ethnicity ^b^ |  |  |  |  |  |  |  |  |  |  |  |  |  |  |
| Asian | 37.5 | (1.4%) | 71.1 | (3.1%) | 619.4 | (20.6%) | 143.0 | (8.6%) | 305.7 | (13.1%) | 37.8 | (1.5%) | 685.1 | (20.6%) |
| Black | 13.6 | (0.5%) | 22.7 | (1.0%) | 407.2 | (13.5%) | 331.8 | (19.9%) | 398.1 | (17.1%) | 7.8 | (0.3%) | 218.4 | (6.6%) |
| Mixed | 11.2 | (0.4%) | 17.5 | (0.8%) | 73.5 | (2.4%) | 21.5 | (1.3%) | 62.0 | (2.7%) | 15.0 | (0.6%) | 43.2 | (1.3%) |
| White | 2437.8 | (90.0%) | 1898.5 | (82.5%) | 1485.8 | (49.4%) | 1073.0 | (64.4%) | 1263.4 | (54.3%) | 2054.5 | (83.2%) | 2183.4 | (65.7%) |
| Other | 8.0 | (0.3%) | 14.3 | (0.6%) | 272.1 | (9.0%) | 31.7 | (1.9%) | 166.7 | (7.2%) | 11.8 | (0.5%) | 91.9 | (2.8%) |
| Missing ^c^ | 202.0 | (7.5%) | 277.0 | (12.0%) | 149.0 | (5.0%) | 64.0 | (3.8%) | 130.0 | (5.6%) | 341.0 | (13.8%) | 103.0 | (3.1%) |
| IMD, index of multiple deprivation; IQR, interquartile range   1. Age in years at first offered appointment. 2. Ethnicity is estimated based on the LSOA of women’s residential postcode, not of individual woman. See [appendix](#_Estimating_ethnicity_by) for further detail. 3. Women whose LSOA was unable to be linked to identify residential region. 4. Dudley, Wolverhampton, and Southwest Staffordshire. | | | | | | | | | | | | | | |

(a)

(b)

**Supplementary Figure 1** Proportion of women attending within 120 (a) and 210 (b) days since letter printed by invitation strategy. The red dotted line indicates the 70% uptake target as set by the NHS breast screening programme.

[figure not shown]

**Supplementary Figure 2**: Proportion of 90-day attendance by service and invitation strategy. Percentage non-White was an estimate based on area-level ethnicity. The Lower Super Output Area (LSOA) code linked to the residential postcode of each woman in the study was used to estimate the proportion of each ethnic group within each screening service. Estimates were derived by weighting and summing across LSOAs using three components: (1) the distribution of LSOAs within each service, (2) the ethnic composition of each LSOA, and (3) the proportion of the study population contributed by each service. IMD scores were obtained at the LSOA level (English Indices of Deprivation 2019) and weighted using GP practice registration counts before mapping to screening centres.

**List of changes to the Statistical Analysis Plan**

Update on 10^th^ April 2024

1. The data were planned to be followed until the 31^st^ of January 2024 and be analysed in February and March. In practice, further follow-up was obtained till the 19^th^ of April, and the timing of analysis was till the 3^rd^ of May 2024.

# Introduction

Attendance in the UK NHS Breast Screening Programme has previously exceeded 70% on average. In the past, women initially received a timed appointment as their first invitation, followed by either a 2^nd^ timed appointment or an open invitation for women who did not attend their first appointment. Previous work showed that a second timed appointment letter was effective at improving screening participation^1^. However, during the Covid pandemic open invitation letters were used routinely to help the screening services to recover more quickly^2^. With the NHS breast screening services (NHSBSP) moving to a new IT system, open invitation letters with online and phone booking are planned to be used as standard from 2024/25.

This study has been commissioned to evaluate the effect of different combinations of timed appointments and open invitations on attendance rate at the NHS Breast Screening Programme. Below describes the statistical analysis plan for the evaluation of the effect of different strategies, either timed or open appointments, for the first invitation, or second invitation for non-attenders.

# Study details

## Objectives

The primary objectives are to evaluate:

1. the effect of different combinations of timed appointments and open invitations on attendance in the NHS Breast Screening Programme; and

2. the effect as above in subgroups defined by index of multiple deprivation (IMD), and area-level summaries of ethnic diversity.

## Design

To meet these objectives, an evaluation was run to compare four strategies:

1. Timed for both first and second invitation (TT),
2. Open invitations for both (OO),
3. Timed followed by Open invitation (TO), and
4. Open followed by Timed invitations (OT).

Women were allocated to each strategy based on whether certain digits in their screening identifier (SX) and NHS number were even or odd (quasi-randomisation as shown in figure 1 of the evaluation protocol for randomisation procedure).

## Setting

The evaluation took place in 8 national Breast Screening Program services:

1. Central and East London (pilot area where the study was first run) (FLO),
2. Outer Northeast London (FBH),
3. North London (EBA),
4. Cambridge (DCB),
5. North and East Devon (LED),
6. Doncaster (CDO),
7. Dudley, Wolverhampton, and Southwest Staffordshire (MDU), and

These services were selected to ensure socio-economic and cultural diversity and included several areas with lower attendance than average in England.

## Inclusion / exclusion criteria

Women within the above services were eligible for this evaluation if they were due to be invited for their next breast screening appointment during the study period. Exclusions were made based on five criteria (as of section 5.2 of the evaluation protocol):

1. Opted out of the screening programme.
2. Require special appointments that require different types of clinics.
3. Self-referred for screening.
4. Women on an early recall protocol.
5. Women who are invited because they are high risk.

## Follow-up

Attendance assessed from date of invitation until the end of January 2024 (data extraction date).

## Primary Endpoint

The 90-day attendance rate. This is defined as attending the originally offered screening appointment, or an alternative appointment within 90 days of the original. For open invitations, the originally offered date is the date of the holding clinic, into which women were booked at the time of sending the first open invitation letter.

## Secondary Endpoints

The 180-day attendance rate, defined as attending the originally offered screening appointment, or an alternative appointment within 180 days of the original. For open invitations, the originally offered date is the date of the initial holding clinic, into which women were booked at the time of sending the first open invitation letter.

## Subgroups

Subgroups for reporting are below, further details are in [section 3.2.1](#source_data_variable) and [section 3.2.2](#derived_variables):

1. IMD (quintile):
   - 1: most deprived
   - 2
   - 3
   - 4
   - 5: least deprived
2. Ethnicity(area-level):

- White
- Non-white

1. Combination of prevalent/incidence screen and binary age categories:
   - Prevalent and under 60
   - Incident and under 60
   - Age 60 and over
2. Screening services:
   - Central and East London (pilot area where the study was first run)
   - Outer Northeast London
   - North London
   - Cambridge
   - North and East Devon
   - Doncaster
   - Dudley, Wolverhampton, and Southwest Staffordshire
   - East Lancashire
3. Rurality of the screening site:
   - Rural
   - Urban
4. Mobility of the screening clinic:
   - Static, e.g. hospital
   - Mobile, e.g. van

Our focus lies in the first two subgroups, IMD quintiles and the area-level ethnicity.

## Sample Size Justification

We aimed for a sample size of 16,000 women for the following reasons.

Previous results comparing timed to open invitations suggest an absolute 8% increase in participation with timed appointments compared to open invitations. As noted above, there is an interest in subgroup analyses. For a comparison of two groups with participation rates of 65% and 73%, 524 persons per group would give 80% power to detect this difference as significant at 5% level with two-sided testing. To allow for estimation of the primary outcome in socioeconomic and ethnic subgroups, we planned to evaluate 16,000 women in total (4,000 per arm).

## Timing of analysis

Data will be analysed in February and March 2024. The statistical analysis will be performed at the Centre for Cancer Screening, Prevention and Detection, Wolfson Institute of Population Health, Barts and The London School of Medicine and Dentistry, Queen Mary University of London.

# Study data

A list of variables will be extracted according to the study protocol, the full list is presented in [section 7.3](#list_all_vars) in the appendices.

* In this document, names of variables will be in *italic* format.

## Preparing data for analysis

- The source dataset from each service has the same format and variables. To prepare a master file of all services the separate extracts must be joined together, with a new file to indicate which service each extract was from.

STATA command **Append** and **generate** a new variable *service* to indicate the source screening service.

- The joined dataset has each line representing one appointment, not per woman. To restructure the data so that each line represents a woman.

STATA command **reshape** from long to wide format using a unique identifier variable (*uniqueid)* and a variable tag each appointment (*[appointmenttag](#appointmenttag_create)*).

Record the total number of women in the final sample. ^1^

- Exclude all screenees who has special requirement based on [exclusion criteria](#inclusion_exclusion_criteria).

**Drop** if ‘Y’ in *specialrequirement.* Record the number of women in this group.^1^

- To assess for risk of bias later, ensure to flag all screenees with administrative errors, e.g. when a wrong type of invitation letter was sent (‘Y’ in *flag2oiinviteandnotaoicl* or in *flag3tabutanoiletterused)*, and keep a record of this number in each arm.^1^

## Variables for analysis

### From source data

The subset of variables from source dataset to be used for our analysis are:

| Variable | Definition | Notes |
| --- | --- | --- |
| *Lsoacode* | Lower Layer Super Output Areas | For various data linkage with census data for demographic profile. |
| *Uniqueid* | Unique patient ID | Generated internally by BSS in place of screening id, unique across the national dataset. |
| *Ageatfoa* | Age at first offered appointment in the screening episode | Range expected [48,70]. |
| *attendedappointment* | Whether an appointment has been attended in this episode | This indicates whether a woman attended her appointment but not whether she was screened. Sometimes women turn up and are not screened for reasons such as, they recently had a mammogram, or they decided not to be screened after arrival. |
| *Screeningdate* | Date of the screening | Empty if not screened. |
| *previousscreeningdate* | The date of previous screening | For incident screenees only. |
| *Armname* | Arm of the study | - 1: OI/OI, - 2: OI/TA, - 3: TA/OI, and - 4: TA/TA. |
| *prevalentincidentstatus* | Prevalent or incidence screening episode | - I: incident, episode complete, - P: prevalent, episode complete, - XI: incident, episode yet to complete, and - XP: prevalent, episode yet to complete. |
| *Date* | Date of the appointment offered/booked | For open invitation, this is an assumed appointment date in a holding clinic. |
| flag2oiinviteandnotaoicl | Flag for when an open invitation letter was used when it should not be | For assessing the risk of bias. Should mostly be missing. |
| flag3tabutanoiletterused | Flag for when a timed appointment letter was used when it should not be | For assessing the risk of bias. Should mostly be missing. |
| *Locationnature* | Whether the clinic was static (hospital) or mobile (van) |  |

### Data linkage and variable derivation

The following variables are derived based on the source data.

| Variable | Definition | Notes |
| --- | --- | --- |
| *service* | Screening service | - Derived from service of which each data was extracted from: - 1, Central and East London (pilot area). - 2, Outer Northeast London. - 3, North London. - 4, Cambridge. - 5, North and East Devon. - 6, Doncaster. - 7, Dudley, Wolverhampton and Southwest Staffordshire, and - 8, East Lancashire. |
| *appointmenttag* | Tag each appointment, in the chronological order of appointment date. | Derived from *date*, labelled 1, 2, 3, etc by the chorological order of each appointment offered/ booked.  For reshaping data between wide and long format, each line represents either an appointment or per woman. |
| *flagadminerror* | Flag for administrative errors that wrong type of invitation letter was sent. | Derived from *flag2oiinviteandnotaoicl* and *flag3tabutanoiletterused.*   - 1, if Y on either variable above, error. - 0, otherwise, no error.   Should be a very small proportion of the sample. |
| *90dayattend* | Primary endpoint, 90-day attendance since first offered appointment | Derived from *attendedappointment and date*.   - 1, if Y on *attendedappointment* and the difference between variable screeningdate and variable *date* is less than or equal to 90 days. - 0, if N on *attendedappointment*, or attended but the difference between variable screeningdate and variable date is greater than 90 days: |
| *180_survtime* | Follow-up duration | - If Y on *attendedappointment, then t*he number of days between variable *screeningdate* and variable *date* if it is less than or equal to 180 days. - Otherwise, then *t*he number of days between variable *date* and the 31^st^ of January 2024 or the end of 180-day follow-up, whichever is the first.   As the time of event/censoring time in cox regression. |
| *180dayattend* | Secondary endpoint, 180-day attendance since first offered appointment | - 1, if Y on *attendedappointment* and the difference between variable *screeningdate* and variable *date* is less than or equal to 180 days, or to the 31^st^ of January 2024, whichever is the first. - 0, if N on *attendedappointment*, or attended but the difference between variable screeningdate and variable date is greater than 180 days.   This is the event variable for cox regression. |
| *imdquintile* | Index of Multiple Deprivation in quintiles | First, small area level index of multiple deprivation 2019 (*imddecile*) by linking *lsoacode (*2011) with IMD2019 data^2^, then derive from deciles to quintiles.   - 1 (least deprived) - 2 - 3 - 4 - 5(most deprived) |
| *ethnicity* | ethnicity (area level estimate) | Small area level ethnicity estimate derived by linking source data with the ethnicity data from Office for National Statistics site^3^ with *lsoacode* as identifier, for women from aged 50 and above, by linking LSOA with census data. Expect in 5 major categories:   - - 1, Asian or Asian British   - 2, Black or Black British   - 3, Mixed   - 4, Other ethnic groups   - 5, White |
| *ethnicity_white* |  | - - Derived from *ethnicity* as defined above.   - 1, white   - 0, non-white |
| *rurality* | Whether the screening site is rural or urban. | Derived by linking source data with the data from open geography portal, on ‘Rural Urban Classification (2011) of Lower Layer Super Output Areas in England and Wales”^4^, using *lsoacode* as identifier.   - - 0, rural   - 1, urban |
| *age_prev_status* |  | Derived from *ageatfoa* and *prevalentincidentstatus:*   - - 1, prevalent and under60,   - 2, incident and under60,   - 3, over60, and   If *prevalentincidentstatus* is missing, impute based on *ageatfoa.* |
| *firstarm* | Open invitation or timed appointment at the first invite. | Derived from *armname* |
| *secondarm* | Open invitation or timed appointment at the second invite. | Derived from *armname* |
| Note: when the *lsoacode* cannot be identified in the sourcedate during data linkage, resolve from checking the data file: LSOA (2011) to LSOA (2021) to Local Authority District (2022) lookup for England and Wales. ^5^ | | |

**NOTE:** The original source dataset should not be altered. Any modification to data extract MUST be saved to a separate file.

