## Secondary endpoint methods

The secondary endpoint, the attendance rate at 180 days since first offered, time-to-event analysis using Kaplan Meier (KM) survival analysis will be used. Data need to be first set up to carry out this analysis using (**stset survtime_var, failure(censoring_var)**. A Kaplan Meier graph by study arms will be presented with risk table, using the STATA command ^9^ **sts graph, by(armname) risktable(start_time(interval)end_time)**.

The relative risk between arms will be estimated by dividing the KM results at suitable timepoints, with 95%CI calculated using bootstrap method, non-attendance by the end of follow-up period is considered censored.

The results will be summarized in a table including the relative risk (RR) and 95% CI We conclude the following for:

- RR < 1, the attendance rate is decreased for the considered study arm compared to the reference category.
- RR = 1, no difference between the attendance rate of the considered study arm and the reference category.
- RR > 1, the attendance rate is increased for the considered study arm compared to the reference category.

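### The 90-day endpoint rule has no minimum follow-up: any woman whose window was still open at extraction would be coded as a non-attender

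*SAP*

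**What the plan says.** The Primary Endpoint section gives the 90-day attendance rate as "defined as attending the originally offered screening appointment, or an alternative appointment within 90 days of the original". For an open invitation, the holding-clinic date serves as the original date.

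Section 3.2.2 (Data linkage and variable derivation) turns this into *90dayattend*. A woman scores 1 if she attended and was screened within 90 days. The other branch reads "0, if N on *attendedappointment*, or attended but the difference between variable screeningdate and variable date is greater than 90 days". Neither branch mentions the extraction date or the time elapsed since the offer.

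The Follow-up section fixes a calendar end for everyone: "Attendance assessed from date of invitation until the end of January 2024 (data extraction date". The list of changes records that "further follow-up was obtained till the 19^th^ of April". The primary model (Primary endpoint methods) is a Poisson regression of the number attending with the number invited as offset, so it has no person-time and no censoring.

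The 180-day endpoint is handled differently. In the same table, the follow-up time of a woman without a qualifying attendance is the "number of days between variable *date* and the 31^st^ of January 2024 or the end of 180-day follow-up, whichever is the first". The Secondary endpoint methods then state that "non-attendance by the end of follow-up period is considered censored".

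**The concern.** When follow-up stops on a calendar date, women invited late have less of it. The SAP allows for that at 180 days and makes no matching provision at 90 days. A woman recorded as N on day 40 of her window is unresolved, yet the rule enters her as a definite failure.

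Two things would be at stake if such women existed. Attendance would be understated in the arms and subgroups that contain them. A woman cut off early may also have experienced only her first letter, and TT and TO share a first letter, as do OT and OO. Such women would carry little of the second-letter difference that these contrasts measure. TT vs TO and OT vs OO are the fourth and fifth hypotheses in a sequence that stops at the first non-rejection, so dilution of the fourth could also block the fifth. The secondary comparison of second invitations, TT+OT vs TO+OO, is exposed in the same way.

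**Working it through.** **Inputs from the SAP.** A 90-day window; end of follow-up on 31 January 2024 (Follow-up section) or 19 April 2024 (list of changes); 65% vs 73%, two-sided 5%, 80% power, 524 per group, and 4,000 per arm (Sample Size Justification).

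**Inputs assumed.** f, the share of each arm cut off before the second letter acts; p1, attendance observed in those women, set at 55%; and a 3-point second-letter effect for illustration. None of these is in the SAP.

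**1. The plan's own figure.** With pooled variance and no continuity correction, the mean rate is 0.69:

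n = [1.960 × √(2 × 0.69 × 0.31) + 0.842 × √(0.65 × 0.35 + 0.73 × 0.27)]² / 0.08² ≈ 523.5, which rounds up to 524. The stated number is reproduced and is not in dispute.

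**2. Who would be exposed.** A window is complete only if the first offered date is at least 90 days before extraction.
- 31 January 2024 − 90 days = 2 November 2023.
- 19 April 2024 − 90 days = 20 January 2024.

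Only non-attenders first offered a later date than these would be miscoded.

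**3. Largest effect on a second-letter contrast.** If a share f shows only first-letter attendance p1, the observed rate in an arm is (1 − f) × p + f × p1. The two arms share the first letter and hence p1, so the difference becomes

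(1 − f) × (pA − pB).

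Example with f = 10%: 0.9 × 65% + 0.1 × 55% = 64.0% and 0.9 × 73% + 0.1 × 55% = 71.2%, a difference of 7.2 points.

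| f (assumed) | True 8 points becomes | Power at 524 per group | True 3 points (65% vs 68%) becomes | Power at 4,000 per arm |
|---|---|---|---|---|
| 0% | 8.0 | 80% | 3.00 | 81% |
| 5% | 7.6 | 75% | 2.85 | 77% |
| 10% | 7.2 | 70% | 2.70 | 72% |
| 20% | 6.4 | 59% | 2.40 | 61% |

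At f = 10%, moving p1 between 45% and 60% leaves the 7.2 points unchanged and power at 524 per group between 70% and 71%. At 4,000 per arm, power for the 8-point column stays near 100% throughout.

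**4. Does another rule in the SAP catch these women?** General principles limits the primary analysis to women with complete primary-endpoint data. An N is coded 0, not missing, so that condition does not remove her. A Kaplan-Meier graph of the primary endpoint is planned (Figure 2), but the tested rate ratio comes from the Poisson model.

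**The case against.** The strongest objection is that nothing in the SAP shows that a single 90-day window was open at extraction. No last offered date is given; eligibility is tied to a study period that the protocol, not shown here, may define. This stands.

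A reader might infer from three features that open windows were expected. None of them supports that.
- **Cut-off at 180 days only.** This fits authors who knew that 90 days would be complete for everyone and 180 days would not.
- **The extension to 19 April 2024.** The SAP gives no reason for it. Since 19 April 2024 − 180 days = 22 October 2023, completing the 180-day follow-up explains it equally well.
- **Source codes such as "XI: incident, episode yet to complete".** These describe episode status, and the SAP does not link them to the 90-day window.

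With April follow-up the exposure is narrow. An affected woman would have been offered a date after 20 January 2024, that is, in the last 11 days before the planned extraction or later. The seven services in Supplementary Table 2 total 17,802 women, so f of 5% to 20% would mean about 890 to 3,560 women in that position. Nothing in the SAP suggests so many.

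The factor 1 − f is also an upper bound on the damage. It assumes that truncated women show no second-letter effect, whereas a woman cut off on day 80 may show most of it. Second-letter timing is not stated.

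Allocation by identifier digits should spread truncation evenly over the arms. That limits imbalance but does not prevent dilution, because both arms of a second-letter contrast would lose the same part of their difference.

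Finally, the completeness condition is not entirely idle. A woman recorded as attending but with no screening date fits neither branch of the derivation and could be excluded by it. The condition could also be read as requiring a finished window, but the SAP does not say so.

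**Conclusion.** The written rule is wrong for any woman with less than 90 days of follow-up, and it is inconsistent with how the same table treats the 180-day endpoint. That conclusion rests on the text alone.

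The consequence is conditional. If such women exist, attendance is understated and second-letter contrasts shrink by at most the factor 1 − f. Their number is unknown and may be zero, particularly with data to 19 April 2024. All values of f, p1 and the 3-point effect above are assumptions.

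The stronger reading, that late-invited women were in fact counted as failures and the second-letter results biased, is not supported by the document. Nor is the main TT vs OO comparison under threat. Those arms also differ in the first letter, so the common-p1 formula does not apply to them directly, but even a reduction from 8 to 6.4 points leaves power near 100% at 4,000 per arm. Smaller second-letter effects and subgroups are more exposed. Severity: minor.

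**What to change.** In section 3.2.2, add to *90dayattend* the condition that the first offered (or holding-clinic) date lies at least 90 days before the actual extraction date. Set the variable to missing otherwise. The existing completeness condition then removes these women from the primary analysis, whether or not they attended. Report the number removed per arm, which would be zero if every window had closed.

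The rule is the same in all arms and does not depend on outcome. It costs one line of code and, if any late-invited women are removed, a small loss of precision. If all windows had closed, no result changes and the report simply documents that.

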When looking at the 90- and 180-day attendance over time amongst 4 invitation strategies since the initial appointment, we used 120- and 210-day attendance since the first invitation letter was printed, instead of using the period since the first appointment was offered. This was to account for the fact when women receive an open invitation, she can book an appointment and therefore attend earlier than the date originally assigned to the virtual clinic. i.e. virtual clinics tend to be 4 weeks since the letter sent, and a woman could call to have an appointment the next day from when the letter was received. When a letter was printed, it was expected to be sent the same or the next day and should be received within a week. As the date printed was around 30 days earlier than a virtual clinic could have been, this was added to 90 and 180 days when date of letter printed was used as the starting point for looking at attendance over time.

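### As derived, the 180-day Kaplan-Meier analysis can lose women screened on or before the offered date, and both attendance endpoints miss women who attend but are not screened

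*SAP*

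**What the plan says.** The Primary Endpoint section counts a woman as a success for "attending the originally offered screening appointment, or an alternative appointment within 90 days of the original". Secondary Endpoints does the same at 180 days. For open invitations the reference date is that of the holding clinic.

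Section 3.2.1 (From source data) separates attending from being screened. Of attendedappointment it says "This indicates whether a woman attended her appointment but not whether she was screened", and of screeningdate "Empty if not screened".

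Section 3.2.2 (Data linkage and variable derivation) names attendedappointment and date as the sources of 90dayattend, but its coding rule then uses screeningdate. A woman is coded 0 if she did not attend, "or attended but the difference between variable screeningdate and variable date is greater than 90 days". 180dayattend follows the same pattern. For attenders, 180_survtime is the number of days from date to screeningdate.

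Secondary endpoint methods sets up the survival data with "stset survtime_var, failure(censoring_var", giving no origin or offset. It then says "The relative risk between arms will be estimated by dividing the KM results at suitable timepoints". Tables 3 to 5 take the 180-day results from the Kaplan-Meier graph.

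The supplementary methods note that with an open invitation "she can book an appointment and therefore attend earlier than the date originally assigned to the virtual clinic". For attendance over time they therefore count 120 and 210 days from the print date of the first letter.

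**The concern.** There are two separate gaps between what the endpoints mean and how they are coded.

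**Survival time.** A timed invitation is meant to bring the woman in on the offered date. If she is screened that day, her survival time is 0. An open-invitation woman who books early has a negative time. Stata's stset, with no options, does not treat a record ending at or before time 0 as being at risk. The women removed are all attenders, and their share is likely to depend on the type of invitation. The 180-day contrast would then compare arms from which different fractions of the successes had been removed.

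**Attended but not screened.** Section 3.2.1 says such women exist. They meet the endpoint definition, but they have no screeningdate and so no difference to test. This gap does reach the primary endpoint.

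**Working it through.** **Plan's own figure.** For 65% v 73%, two-sided 5%, 80% power, pooled variance: n = [1.96·√(2·0.69·0.31) + 0.8416·√(0.65·0.35 + 0.73·0.27)]² / 0.08² = (1.282 + 0.548)² / 0.0064, which rounds up to 524 per group, as stated. It is used here only as a source of base rates: 73% v 65%, difference 8.0 points, ratio 1.12.

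**Survival time.** Let a be the share of invitees attending at or before time 0 and b the share attending later by day 180, with no censoring before then. True attendance is a + b. If records at or before time 0 are excluded, the Kaplan-Meier estimate is b/(1 − a). The documents do not give a, so the values below are assumptions. In every row, true attendance is 65% timed and 58% open, true RR 1.12.

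| Timed a + b | Open a + b | Timed estimate | Open estimate | RR |
|---|---|---|---|---|
| 45% + 20% | 20% + 38% | 0.20/0.55 = 36.4% | 0.38/0.80 = 47.5% | 0.77 |
| 25% + 40% | 5% + 53% | 0.40/0.75 = 53.3% | 0.53/0.95 = 55.8% | 0.96 |
| 15% + 50% | 5% + 53% | 0.50/0.85 = 58.8% | 0.53/0.95 = 55.8% | 1.05 |

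The same check on the plan's own rates uses s, the share of attenders at or before time 0, and the estimate p(1 − s)/(1 − ps):

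- s = 75% timed, 25% open: 0.1825/0.4525 = 40.3% v 0.4875/0.8375 = 58.2%, RR 0.69. Of 4,000 per arm, 2,190 and 650 women are dropped.
- s = 50% in both: 0.365/0.635 = 57.5% v 0.325/0.675 = 48.1%, RR 1.19.
- s = 25% timed, 75% open: 0.5475/0.8175 = 67.0% v 0.1625/0.5125 = 31.7%, RR 2.11.

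With s from 25% to 90% (timed) and 10% to 75% (open), the RR runs from 0.34 to 2.11 against a true 1.12. A simulated Kaplan-Meier with 4,000 per arm (s = 75% and 25%) gave 41.2% and 58.5% after exclusion, close to the formula. Keeping everyone gave 73.1% and 65.9%. Adding 30 days to all times and reading at day 210 gave the same 73.1% and 65.9%.

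Reading the number of days as an absolute value does not solve this: same-day attenders still have time 0, and early attenders are placed at the wrong time.

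**Attended but not screened.** Let u be the assumed share of attenders without a screeningdate. If they are coded 0, the recorded rate is p(1 − u):

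- u equal in both arms, 0.5% to 5%: the rates fall to 72.6% and 64.7%, down to 69.35% and 61.75%. The difference is 7.96 to 7.6 points and the ratio stays 1.12.
- u = 2% timed, 0% open: 71.5% v 65%, 6.5 points, ratio 1.10.
- u = 5% timed, 0% open: 69.35% v 65%, 4.4 points, ratio 1.07.

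If they are instead missing and removed, the rate is p(1 − u)/(1 − pu). For u = 2% timed, that is 0.7154/0.9854 = 72.6%, a difference of 7.6 points from 65%.

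**The case against.** The exclusion at time 0 is Stata's default behaviour. The SAP does not state it, and it was not run here. It remains an assumption about the software, though the SAP commits to Stata and gives the command without options.

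The supplement already moves attendance over time to the print date, and Tables 3 to 5 read from a Kaplan-Meier graph. If that graph uses the print-date clock, the problem is avoided. But Secondary Endpoints, section 3.2.2 and Secondary endpoint methods still use the offered date, and nothing ties the tables to the supplement's clock.

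A severe error would be visible. In the first row of the table, 90-day attendance of at least 45% would stand beside a 180-day figure of 36%. That lowers the chance of an unnoticed reversal, but it leaves the repair to be chosen after results are seen.

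The SAP does not say in words that unscreened attenders are coded 0; they fit neither category. The 0 arises because Stata orders missing values above every number. If the code guards against that, the women are missing and fall to the complete-data rule. The SAP sends missing source data to the data team first, but a date that is empty by definition cannot be completed.

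It is also fair that attendedappointment is an episode-level field and that the data dictionary lists no attended-appointment date. The date has to be inferred from the appointment rows.

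A reader might further infer that the planned RR is inverted, because the graph command lacks the failure option and a Kaplan-Meier curve shows those not yet attending. The documents do not support that. The stated reading of the RR and the Table 3 column for 180-day attendance show that attendance is what is divided.

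**Conclusion.** The point holds in two parts of unequal weight.

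The survival-time derivation is the serious one. As written, it gives zero or negative times to women who attended, and the stated command would by default exclude them from the Kaplan-Meier figures and from the 180-day estimates in Tables 3 to 5. The bias in the RR can go either way, and a reversal is possible. Its size rests on shares that the documents do not report, and on stset's default.

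Two stronger conclusions should not be drawn. The timed arms need not be the ones penalised, since early open-invitation attenders are lost too. Nor is the primary Poisson analysis affected by this part: a difference of 0 or less satisfies the 90-day limit, so those women are correctly coded 1.

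The second part does reach the primary endpoint, because women who attended unscreened are never counted as attenders. The effect is probably small if their share is similar across arms, and it matters for the contrast only if the share differs. The documents do not show that it does.

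**What to change.** **Survival clock.** Align section 3.2.2 and Secondary endpoint methods with the supplement in one of two ways, and feed Tables 3 to 5 from the resulting curve:

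- Start the clock in all four arms at the first letter's printed_on date and read at 210 days. State that this only approximates 180 days from the offer, since the gap between printing and clinic is about 30 days.
- Keep the offered date, add one constant to every event and censoring time so that all are positive, and read at 180 days plus that constant. This keeps the defined endpoint exactly.

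**Attendance date.** In 90dayattend, 180dayattend and 180_survtime, use the date of the attended appointment, at least where screeningdate is empty. State how that appointment is picked from the per-appointment rows. Report by arm the number of women who attended without being screened.

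**Optional wording.** Write the RR as the ratio of (1 − KM) and add the failure option to the graph command.

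The cost is rewording three variable definitions and one methods paragraph, then rerunning the code. The print and appointment dates are in the extract. The attended-appointment rule needs some care where a woman has several appointments.
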